### Study design

A double-blinded randomized controlled crossover trial will be conducted and all participants will undertake rTMS-active and sham. Group 1 will start with five sessions of rTMS-active. After two weeks, this group will be reallocated to five sessions with rTMS-sham. In contrast, group 2 will do the opposite protocol (participants will start allocated to five sessions of rTMS-sham, and after a two-week washout period will be reallocated to five sessions of rTMS-active). The two-week washout period has been used in some studies [24, 27] and was shown to be enough to reset the effects of the first five sessions, considering that the motor effects of the rTMS in individuals with iSCI are sustained for 1 h [24] to two weeks [14] and that spasticity effects endure for one week [16, 23]. Figure 1 summarizes the planned experimental design. This research protocol follows the SPIRIT recommendations. For the SPIRIT Checklist see Additional file 1 and for the SPIRIT Figure see Fig. 2. Table 1 provides an overview of the trial characteristics, based on the WHO Trial Registration Data Set.

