**Fig. 1 Fig1:**
[figure not shown]
*Flowchart* for the rTMS study protocol. The participants will be selected and the eligibility assessment will be applied. They will then be randomized and allocated to group 1 (starting with rTMS-active) or group 2 (starting with rTMS-sham). Five sessions of rTMS-active and sham will be applied to participants in each group over one week, with a washout period (two weeks). Assessments will be before and after each intervention period (i.e. sham and active) using the motor and sensory scales, spasticity scale, and surface electromyography

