**Fig. 2 Fig2:**
[figure not shown]
SPIRIT figure. Description of the rTMS study protocol

**Table 1 Tab1:** Trial characteristics based on WHO Trial Registration Data Set

Data category	Trial information
Primary registry and trial identifying number	ClinicalTrials.gov, ID: NCT02899637
Date of registration in primary registry	25 August 2016 on
Secondary identifying numbers	Ethical Committee of Paraiba State University, under the number CAEE: 18753713.0.0000.5187
Source(s) of monetary or material support	Foundation of Support for Research of São Paulo State - FAPESP #2015/13096-1 and Coordination for Higher Education Staff Development - CAPES.
Primary sponsor	University of Sao Paulo – USP
Secondary sponsor(s)	NA
Contact for public queries	[name], [name]
Contact for scientific queries	[name], [name]
Public title	Effects of transcranial magnetic stimulation on incomplete spinal cord injury
Scientific title	Effects of high-frequency transcranial magnetic stimulation on functional performance in individuals with incomplete spinal cord injury: study protocol for a randomized controlled trial
Country of recruitment	Brazil
Health condition(s) or problem(s) studied	Spinal cord injury
Interventions	High-frequency repetitive transcranial magnetic stimulation on the lower-limb area of the motor cortex, over one week (five consecutive sessions – once a day)
Key inclusion and exclusion criteria	Inclusion criteria: clinical diagnosis of iSCI with non-progressive etiology; at least six months post iSCI; clinical stability; age range 18–60 years; satisfactory score in Scale of Mini-Mental State Examination (i.e. cut-off points of 13 for illiterates, 18 for low and middle school, and 26 for high school); no pathological alterations on electroencephalography; absence of depression as assessed by the Hamilton Depression Scale and receive sensorimotor conventional physiotherapy. Exclusion criteria: metal prosthesis in some part of the body; cardiac pacemaker; either cognitive impairment, psychotic, or either schizophrenic disorders; neuropsychiatric co-morbidity; drugs that reduce seizure threshold or spasticity
Study type	Interventional allocation: randomized
	Masking: double-blind
	Assignment: crossover
	Primary purpose: treatment
Date of first enrolment	December 2017
Target sample size	20
Recruitment status	Recruiting
Primary outcome(s)	Change in motor scores from baseline to four weeks

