### Randomization

Participants will be randomly allocated to either group 1 (rTMS-active) or group 2 (rTMS-sham) with a 1:1 allocation defined by a computer-generated randomization using the R package (R Foundation for Statistical Computing) [32]. Randomization will be under the control of a blinded investigator who will be the only person allowed to manage the electronic security file of the randomization to assign the individuals. The investigator will be blind to the group in which the participant is allocated to.

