#### Data analysis

The analysis will follow a pre-specified analysis plan, based on comparing the groups as randomized (intention-to-treat). All data will be presented as mean ± standard deviation and summarized in frequency tables. We will use Microsoft Office Excel for Windows (version 2013) to store the data and the Statistical Package for Social Sciences (SPSS-IBM®) version 21 for Windows to perform statistical analysis. The normality and homogeneity of all variables (i.e. primary and secondary outcomes) will be tested with the Shapiro–Wilk and Levene’s test, respectively. For non-parametric data, the Friedman test will be used followed by the Wilcoxon post hoc test. We will use the ANOVA two-way (2 × 4) for the inferential statistic of the parametric data, with Tukey’s post hoc tests. Significance level will be set as α ≤ 0.05 and the effect size will be calculated by eta-squared (*ŋ*
^*2*^).

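### On its best-fitting reading, the planned 2 × 4 ANOVA has no term that isolates active from sham stimulation; the crossover treatment contrast should be named as the primary test

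*Protocol article*

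**What the plan says.** The Data analysis section fixes the parametric method: "We will use the ANOVA two-way (2 × 4) for the inferential statistic of the parametric data", followed by Tukey comparisons, with eta-squared as the effect size. It describes the analysis as "based on comparing the groups as randomized (intention-to-treat"). Its non-parametric route is: "For non-parametric data, the Friedman test will be used followed by the Wilcoxon post hoc test". It names neither ANOVA factor, does not say whether the ANOVA is repeated-measures, and names no treatment contrast.

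Other sections define the layout:

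- Study design: "all participants will undertake rTMS-active and sham". Group 1 starts on active, and then "After two weeks, this group will be reallocated to five sessions with rTMS-sham". Group 2 does the reverse.
- Caption of Fig. 1: "Assessments will be before and after each intervention period (i.e. sham and active"). That makes two assessments in each of two periods, four in all.
- Randomization: "Participants will be randomly allocated to either group 1 (rTMS-active) or group 2 (rTMS-sham"). The labels are those of a parallel-group trial, although both groups receive both conditions.
- Table 1, primary outcome: "Change in motor scores from baseline to four weeks".

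**The concern.** In an AB/BA crossover the randomised group is an order of treatments, not a treatment. An analysis built on comparing those groups answers a different question from the one the trial asks. The Abstract and the Discussion both name the effect size of rTMS as something the trial is to assess, so the plan should point to one quantity that is that effect. If none is named, the analyst must choose among two main effects, an interaction and many post hoc pairs once results are in. An eta-squared for any of the three terms could then be read as the effect of stimulation when it is not.

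**Working it through.** **1. The plan's own figure.** The only power figure is in the Sample size section: 14 participants for power 0.80, alpha 0.05 and Cohen's *d* 0.65, raised to 20. It does not identify the test.

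- A paired two-sided *t* test with 0.65 on the within-person difference needs 21.
- If 0.65 is on the raw scale with an assumed correlation of 0.7, the standardised difference is 0.65/√(2 × 0.3) = 0.839, and 14 suffice.
- The between-group main effect of a 2 × 4 repeated-measures ANOVA, with 0.65 entered as *f* and correlation 0.5, also gives 14.

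So the sample size cannot settle what the factors are.

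**2. Which 2 × 4?** The design supplies two groups and four assessments. Treatment by pre/post would be 2 × 2. Group × assessment therefore fits best, but it is an inference.

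**3. What each term estimates.** Let δ be the effect of active at the end of its period, with no carryover, and t1 to t4 common time effects.

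| | Pre 1 | Post 1 | Pre 2 | Post 2 |
|---|---|---|---|---|
| Group 1 | t1 | t2 + δ | t3 | t4 |
| Group 2 | t1 | t2 | t3 | t4 + δ |
| Group 1 − Group 2 | 0 | δ | 0 | −δ |

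- Group main effect: (δ − δ)/4 = 0. It carries no treatment information.
- Assessment main effect: t1, t2 + δ/2, t3, t4 + δ/2. Treatment and time are mixed.
- Interaction: the pattern (0, δ, 0, −δ), tested on 3 df.
- Treatment contrast: ½[(Group 1 Post 1 − Post 2) − (Group 2 Post 1 − Post 2)] = ½[(δ + t2 − t4) − (−δ + t2 − t4)] = δ. It uses four cells. Eight cells give 8 × 7/2 = 28 Tukey pairs, and no single pair is this contrast.

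**4. Power at N = 20 (10 per sequence).** Assumptions not in the documents: 0.65 is in raw-score SD units, compound symmetry, no carryover, within-person correlation ρ. At ρ = 0.5 the SD of a within-person difference is √(2 × 0.5) = 1, so 0.65 is then also the effect on the within-person difference.

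- Single contrast at ρ = 0.5: standard error ½√(1/10 + 1/10) = 0.2236; 0.65/0.2236 = 2.907; squared, 8.45, on 1 and 18 df.
- Repeated-measures interaction at ρ = 0.5: noncentrality 10 × 2 × (2 × 0.65²/4)/(1 − 0.5) = 8.45, on 3 and 54 df.

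The signal is the same, but the interaction spreads it over three degrees of freedom. Noncentral *F* gives 0.785 and 0.646. Separate simulations gave 0.78 to 0.79 and 0.64 to 0.65.

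| Test | ρ = 0.5 | ρ = 0.7 | ρ = 0.9 |
|---|---|---|---|
| Single contrast, post-period scores | 0.78 | 0.94 | 1.00 |
| 3-df interaction, repeated measures | 0.65 | 0.87 | 1.00 |
| 3-df interaction, no participant term | 0.23 | 0.16 | 0.09 |
| Group main effect, repeated measures | 0.05 | 0.05 | 0.05 |
| Single contrast, change from each period's baseline | 0.50 | 0.71 | 0.99 |

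Without a participant term, the group test also rejects about 27% of the time under the null at ρ = 0.7. With 14 completers and ρ = 0.5, the single contrast has power 0.61 and the repeated-measures interaction 0.46.

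**5. Baseline adjustment in the replacement model (0.65 on the within-person difference, N = 20, error SD 1).** Adding the raw pre-period score alongside a random participant effect gave power 0.71 to 0.74 at between-person SD 1, and 0.54 to 0.57 at SD 3. The second range is below the interaction's 0.64. Adjusting instead for the within-participant difference of the two pre-period scores gave about 0.76.

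**The case against.** The factors are unnamed, and the article refers to a pre-specified analysis plan that may name them along with error terms and contrasts. If the four levels were pre- and post-active and pre- and post-sham, a post hoc pair would compare active with sham directly, though still without a period term. This stands as a limit: group × assessment is the best-supported reading, not a quotation. It does not dispose of the point, because the article itself states the test, its dimensions, the post hoc method and the comparison of randomised groups, and these do not match the design.

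A reader might infer that the plan cannot estimate the treatment effect at all. The documents do not support that. The effect is a contrast within the interaction, and some Tukey pairs do compare active with sham, for example group 1 with group 2 after period 1. Likewise, the change at four weeks is taken once both groups have had both conditions. Without carryover, the group difference in that change still compares active with sham, but between participants and from the second period only.

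A reader might also infer that the crossover's efficiency is thrown away. That needs an ANOVA with no participant term. The Friedman and Wilcoxon alternatives are within-participant tests, which suggests that the parametric counterpart is repeated-measures too. Levene's test does not show otherwise, because a mixed ANOVA also assumes equal variances across groups.

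Finally, a reader might fear that drift over time will be reported as efficacy. Nothing in the article says that the time effect will be used in that way. Participants must be clinically stable and are withdrawn if their rehabilitation changes, and no drift is given from which to size the risk.

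**Conclusion.** The concern holds in limited form. On the reading that best fits the design, the stated ANOVA does not isolate active versus sham, and eta-squared for any of its terms is not the treatment effect size that the trial aims to assess. If the ANOVA is repeated-measures, the loss of power is moderate: about 0.64 to 0.65 against 0.78 to 0.79 at correlation 0.5, 0.87 against 0.94 at 0.7, and none at 0.9. It is severe only for the group comparison (about 0.05 in a repeated-measures model) or for an interaction tested without a participant term (0.23 or less).

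These figures assume 20 completers, a 0.65 SD effect, compound symmetry and no carryover. The article gives 0.65 as Cohen's *d* without saying which SD it refers to, and it gives no correlation. The identification of the terms does not depend on the effect size or the correlation. That the group effect carries no treatment information does depend on there being no carryover.

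**What to change.** Replace the omnibus-and-Tukey route for the primary outcome before the data are analysed:

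- Analyse the end-of-period ASIA motor scores with treatment, period and sequence as fixed effects and participant as a random effect.
- Name the single active-minus-sham contrast as the primary test, reported with its 95% CI in ASIA points.
- Do not add the raw pre-period score as a covariate alongside the random participant effect. If baseline adjustment is wanted, use the within-participant difference of the two pre-period scores.
- Say how this contrast relates to the baseline-to-four-weeks outcome in Table 1, and describe groups 1 and 2 as sequences in the Randomization section.
- State that the effect-size scale, the within-person correlation and the absence of carryover are assumptions.

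The cost is analysis wording only. The same assessments and participants are used, and the model can be fitted in standard mixed-model software.

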### Statistical analysis

#### Sample size

The sample size was calculated using statistical software (GPower 3.1.5) [57] on the main outcome measure (i.e. the motor score). This calculation was based on data from one study with a group of SCI individuals that received high-frequency rTMS at a frequency of 5 Hz on the vertex, which related to an improvement in clinical measures of the motor score [24]. The power was 0.80; the alpha was 0.05, the effect size was 0.65 (Cohen’s *d*). The sample estimation indicated that 14 participants would be necessary (i.e. seven per group). With an adjustment to allow for a dropout rate, we will recruit 20 participants.

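### The parametric branch names a two-way 2 × 4 ANOVA with Tukey tests for four correlated scores per participant and states no within-participant error term

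*Protocol article*

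**What the plan says.** The Study design section describes a crossover in which everyone receives both active and sham stimulation. The Fig. 1 caption fixes the measurement times: "Assessments will be before and after each intervention period". With two periods, that makes four scores per participant.

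The Data analysis section sends each outcome down one of two branches after a normality check. For non-parametric data, "the Friedman test will be used followed by the Wilcoxon post hoc test". For parametric data it names a two-way 2 × 4 ANOVA "for the inferential statistic of the parametric data, with Tukey’s post hoc tests". The two factors are not labelled. The reading that fits the design is two sequence groups by four assessments. Neither a repeated-measures or mixed form nor an independent-observations form is stated.

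**The concern.** Friedman and Wilcoxon compare scores within the same person. A two-way ANOVA with no participant term, followed by Tukey's test in its standard form, compares independent means. The same four scores would therefore be handled under two different data structures, with a normality test choosing between them.

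This is more than a detail left to a fuller plan. The procedure is named, it is the only parametric analysis given for the primary motor score, and it does not fit the design. In a trial of 20 people, the wrong error could turn a chance difference between the sequence groups into a significant result. It could also hide a real change after active stimulation.

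**Working it through.** **Inputs from the protocol article.** Two groups of 10 (Abstract), four assessments (Fig. 1 caption), alpha 0.05 (Data analysis) and an effect of 0.65 labelled Cohen's d (Sample size). The within-person correlation ρ is not given, so a range is assumed. The SD behind the 0.65 is not stated either, so two scales are used: the SD of a single score, and the SD of a paired difference.

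**The plan's own figure.** The Sample size section says: "The power was 0.80; the alpha was 0.05, the effect size was 0.65", and arrives at 14 participants. That number does not identify the intended error structure. At d = 0.65 a two-sided paired t test needs 21 participants, and an independent t test needs 39 per group. A repeated-measures ANOVA with f = 0.325, four measures and an assumed ρ of 0.5 needs 16, with power 0.788 at 14. The sample size therefore cannot settle how the ANOVA is meant to be run.

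**Standard errors if no participant term is used.** Take unit score variance and equal correlation ρ between all four scores. The ANOVA treats 20 × 4 = 80 rows as independent, with 80 − 8 = 72 error degrees of freedom.

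- Group effect: the true variance of a group mean is (1 + 3ρ)/40, but the ANOVA uses 1/40. The true SE is √(1 + 3ρ) times the one used: 1.58 at ρ = 0.5 and 1.92 at ρ = 0.9.
- Contrasts between assessments: the true SE is √(1 − ρ) times the one used: 0.71 at ρ = 0.5 and 0.32 at ρ = 0.9.

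**False positives.** For the group test the rate is about 2(1 − Φ(1.99/√(1 + 3ρ))). This gives 21% at ρ = 0.5 and 30% at ρ = 0.9.

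Simulation (at least 20,000 trials per setting, 10 + 10 participants, normal data, equal correlations, no effect):

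| ρ | Group, no participant term | Group × time, no participant term | All three tests, repeated-measures error |
|---|---|---|---|
| 0.5 | 21% | 0.3% | about 5% |
| 0.7 | 27% | under 0.1% | about 5% |
| 0.9 | 31% | 0% | about 5% |
| 0.95 | 32% | 0% | about 5% |

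**Power of group × time.** Add a gain d after active stimulation only, with no carry-over: assessment 2 in group 1 and assessment 4 in group 2. The interaction effects are ±d/2 in four cells, so their squares sum to d². With the repeated-measures error the noncentrality is 10d²/(1 − ρ).

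- Score-SD scale, ρ = 0.5: 10 × 0.4225/0.5 = 8.45, which gives 65% power on F(3, 54).
- Paired-difference scale: d = 0.65 × √(2(1 − ρ)), so the noncentrality is 10 × 0.4225 × 2 = 8.45 at every ρ.

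Simulated power:

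| ρ | No participant term, score-SD scale | No participant term, paired-difference scale | Repeated-measures error, score-SD scale | Repeated-measures error, paired-difference scale |
|---|---|---|---|---|
| 0.5 | 23% | 23% | 64% | 64–65% |
| 0.7 | 16% | 5% | 87% | 64–65% |
| 0.8 | 12% | 0.8% | 97% | 64–65% |
| 0.9 | 8–9% | 0% | over 99% | 64–65% |

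Repeat runs differed by about one percentage point: up to 33% for the group test, and up to 17% for group × time at ρ = 0.7. With seven per group on the score-SD scale, group × time power over ρ 0.5 to 0.9 falls from 13% to 4% without a participant term. With the repeated-measures error it rises from 46% to over 99%.

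**If the ANOVA is read as repeated-measures, but uncorrected.** With assumed correlations of 0.90 to 0.98 within a treatment week and 0.70 to 0.90 across the washout, the time and interaction tests reject in 7.6% to 10.5% of null trials. Under milder patterns (0.90/0.85, 0.85/0.80, 0.80/0.70) they reject in 5.1% to 5.8%. Under the first set, Tukey's pooled error makes the per-pair null rates uneven: at most 0.04% within a week and 2.5% to 3.9% across the washout, against 1.05% nominal.

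**The case against.** The strongest reply is that a 2 × 4 ANOVA is ordinary shorthand for a mixed group × time analysis, and that naming Friedman and Wilcoxon shows the authors regard the scores as repeated. That stands in part. A reader might infer that the plan treats 80 observations as independent, but the text never says so. What it shows is an unstated error structure beside a post hoc test that, in its standard form, is for independent means.

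Four further inferences are not supported:

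- **That Levene's test is an error.** It can validly compare the two sequence groups at each assessment, and the plan does not offer it as a sphericity check.
- **That displayed variability would be wrong.** Only means and standard deviations are planned, and a descriptive SD is unaffected by within-person correlation.
- **That a real gain cannot be detected.** Power below 1% without a participant term appears only from ρ of about 0.8, and only on the paired-difference scale.
- **That Tukey would almost never find a pre/post change under the repeated-measures reading.** The low rates above are null rates. With a gain of 0.65 score SD, Tukey detects the group 1 change in 70% of trials at correlations 0.90/0.70, and in about 100% at 0.98/0.90.

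The absence of a sphericity correction is the kind of detail an article may leave to a fuller plan. It is not counted as a defect here and enters only through the fix.

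**Conclusion.** Wrong as written; should be fixed. Four correlated scores per participant are documented, and the named parametric procedure carries no participant term. Run that way, the group test has about 21% to 32% false positives at ρ from 0.5 to 0.95. The group × time test has at most about 23% power, against 64% or more with the repeated-measures error.

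These sizes rest on assumed equal correlations, normal data, no carry-over and 10 participants per group. The direction does not depend on the exact ρ: any positive correlation makes the group test too liberal and the within-person tests too conservative. If the authors already intend a mixed ANOVA, most of this resolves once they say so, and the choice of Tukey for comparisons between assessments remains to be changed.

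**What to change.** Replace the parametric sentence in Data analysis with one that states the error structure. For example: *normally distributed outcomes will be analysed with a repeated-measures (mixed) ANOVA or linear mixed model in SPSS, with sequence group as the between-participant factor, assessment as the within-participant factor and participant as the subject; comparisons between assessments will be paired contrasts with Holm adjustment.* If the repeated-measures ANOVA is chosen, add the Greenhouse–Geisser correction. An unstructured covariance in a mixed model is optional: it has ten parameters to estimate from at most 20 people.

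The cost is wording and a different procedure in the software already named. No extra data or participants are needed. Error degrees of freedom fall from 72 to 54 (18 × 3) for time and group × time, and to 18 (20 − 2) for the group effect.

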**Methods:**

A double-blind randomized sham-controlled crossover trial will be performed by enrolling 20 individuals with incomplete SCI. Patients who are at least six months post incomplete SCI (aged 18–60 years) will be recruited through referral by medical practitioners or therapists. Individuals will be randomly assigned to either group 1 or group 2 in a 1:1 ratio, with ten individuals in each group. The rTMS protocol will include ten sessions of high-frequency rTMS (5 Hz) over the bilateral lower-limb motor area positioned at the vertex (Cz). Clinical evaluations will be performed at baseline and after rTMS active and sham.

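### The only planned follow-up to the 2 × 4 ANOVA is Tukey's all-pairs test, which does not isolate active versus sham, and the sample size makes no allowance for it

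*Protocol article*

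**What the plan says.** **Sample size.** The calculation is on the motor score: "The power was 0.80; the alpha was 0.05, the effect size was 0.65", the last figure labelled Cohen's d. The result is: "The sample estimation indicated that 14 participants would be necessary (i.e. seven per group". Then: "With an adjustment to allow for a dropout rate, we will recruit 20 participants". The section names the software but not the test, its sidedness, the number of comparisons or any correlation between repeated scores. It mentions no multiplicity adjustment.

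**Data analysis.** Parametric outcomes go to a two-way (2 × 4) ANOVA at a significance level of 0.05, which serves "for the inferential statistic of the parametric data, with Tukey’s post hoc tests". The section does not name the two factors, the set of means that Tukey covers, or a contrast that carries the active-versus-sham question. Non-parametric data go to Friedman and Wilcoxon tests instead.

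**Design.** Study design and the legend of Fig. 1 describe a two-sequence crossover. Each person receives both active and sham, with an assessment before and after each period, so there are four assessments. The Abstract gives the allocation: "randomly assigned to either group 1 or group 2 in a 1:1 ratio, with ten individuals in each group". The natural reading of 2 × 4 is therefore sequence group by assessment.

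**The concern.** Tukey's procedure controls the error rate over every pair in its family: 6 pairs among four means, or 28 among eight cells. Most of those pairs, such as one pre-treatment score against another, say nothing about active versus sham. The comparison of interest pays for them all, while the sample size shows no sign of having budgeted for that.

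The second problem is structural. A crossover answers its question through one within-person contrast, and the planned analysis never tests that contrast by itself. The omnibus F is too broad, and the Tukey pairs are the wrong comparisons.

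At stake is an avoidable false negative in a 20-person trial that is meant to clarify inconsistent evidence. A significant F whose source cannot be assigned to treatment would be equally unhelpful.

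**Working it through.** **1. The plan's own figure.** The inputs from Sample size are power 0.80, alpha 0.05 and d = 0.65. I used the exact noncentral t.
- Paired test, two-sided, ncp = 0.65√n: 80% power needs n = 21. At n = 14, power is 61.4%.
- Paired test, one-sided: n = 17, with 74.5% at 14.
- Two-sample test, two-sided: 39 per group, with 20.2% at 7 per group.
- Repeated-measures ANOVA interaction with f = 0.65/2 = 0.325, 2 groups, 4 measures and an assumed correlation of 0.5: N = 16, with 78.8% at 14.
- Between-group factor with 0.65 entered as f rather than d, same settings: N = 14 (80.6%).

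So 14 does not follow from a single two-sided comparison at d = 0.65. The closer matches need inputs that the article does not give.

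**2. Where active versus sham sits in a 2 × 4 table.** Write A1–A4 for the four assessment means in group 1 (active first) and B1–B4 for those in group 2 (sham first). The within-person effect averaged over sequences is

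½{[(A2 − A1) − (A4 − A3)] + [(B4 − B3) − (B2 − B1)]}.

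- All eight cells have non-zero weight. A Tukey pair has two, so this contrast is not one of the 28 cell pairs.
- It is not one of the 6 pairs of assessment means either. Each of those means averages both groups, so the second assessment mixes people who have just had active with people who have just had sham.
- It is one direction within the group-by-assessment interaction, which has (2 − 1)(4 − 1) = 3 df. A significant F on 3 df could also reflect carry-over or another difference between sequences.

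**3. Size of the correction when a pair stands in.** For the illustration, suppose the four levels are recoded by condition (before and after active, before and after sham), so that after-active against after-sham is a pair. Assume 0.65 is its standardised paired difference. The Tukey critical value on the t scale is q(0.95; k, df)/√2, with df = 3(n − 2).
- n = 20, k = 4, df = 54: 3.749/√2 = 2.651, per-pair two-sided alpha 0.0105.
- n = 14, k = 4, df = 36: 3.809/√2 = 2.693, per-pair alpha 0.0107.

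**4. Power under those assumptions.** ncp is 0.65√20 = 2.907 and 0.65√14 = 2.432.

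| Completers | Single two-sided 0.05 test (df n − 1) | Tukey, four means |
|---|---|---|
| 20 | 78.7% | 60.3% |
| 14 | 61.4% | 40.9% |

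Using 19 df at n = 20 instead of 54 gives 54.9%. For 80% power, Tukey over four means needs 29 completers, against 21 for the single test. A family of three means gives 64% to 69% at n = 20, depending on the df.

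**5. Sensitivity to the meaning of d.** If 0.65 is on the raw SD, the paired effect is 0.65/√(2(1 − r)), where r is the within-person correlation, which the article does not state. At 20 completers:

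| r | Paired effect | Single test | Tukey, four means |
|---|---|---|---|
| 0 | 0.460 | 49.7% | 28.6% |
| 0.3 | 0.549 | 64.5% | 43.0% |
| 0.5 | 0.650 | 78.7% | 60.3% |
| 0.7 | 0.839 | 94.5% | 86.0% |

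At 14 completers and r = 0.7, the figures are 82.7% and 67.1%. The level depends on r. In every row Tukey is below the single test.

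**The case against.** The strongest reply is that the ANOVA, not Tukey, is the named inferential test, and Tukey only follows it. On the interaction reading (f = 0.325, correlation 0.5), omnibus power at 20 is about 93%. That stands as far as it goes: 60% is not the power of the analysis as a whole. But rejecting a 3-df interaction does not show that active beat sham, and the only step named for locating the effect is Tukey.

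A reader might also infer that the sample size assumed one comparison at 0.05, so that the powered test and the planned test demonstrably differ. The documents do not support that. No test is named, a single two-sided comparison does not yield 14, and some ANOVA settings come closer. What can be said is that the effect size is a two-mean measure and no multiplicity allowance is stated.

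Nor may one say that the trial has 60% power instead of the stated 80%. The 80% is attached to 14 participants, and 20 is the figure after a dropout allowance. The 60% also depends on family size, correlation and coding, none of which is given. At a correlation of 0.7 with d on the raw SD, Tukey power at 20 exceeds 80%.

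Eight-cell figures should not be used for a 20-person comparison, because each cell holds only ten people.

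Finally, the article refers to a pre-specified analysis plan that is not shown, and that plan may name the primary contrast. The point here rests on the method the article does fix, not on missing detail. It concerns the parametric branch only.

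**Conclusion.** The point holds in a limited form. The parametric analysis, as stated, has no step that tests active against sham directly. Its one follow-up procedure spends error control on pairs that do not bear on the question, and the sample size shows no allowance for this.

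The firm parts are the structure, which follows from reading 2 × 4 as sequence by assessment, and the direction of the power loss. The size is conditional. With a paired standardised difference of 0.65 and a four-mean family, the loss is about 18 percentage points at 20 completers and about 20 at 14. With d on the raw SD, it runs at 20 completers from about 21 points (correlation 0 or 0.3) to about 8 or 9 (correlation 0.7).

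That 14 cannot be reproduced from d = 0.65 by a single two-sided test is a separate defect. Removing Tukey does not cure it.

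**What to change.** In Data analysis, name one primary test: the within-person active-minus-sham contrast of change in ASIA motor score, estimated across both sequences with period accounted for, at two-sided 0.05. Keep Tukey for the remaining pairs of assessments and label those results descriptive.

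If Tukey is kept for the primary comparison, restate the power in Sample size for that corrected test, giving the family size and the assumed within-person correlation. Do not insert a fixed 60%, which holds only under the illustration's assumptions.

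The cost is a sentence or two of analysis wording, with no extra patients, visits or data. The small downside is that the other pairwise comparisons become descriptive.
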